#### Secondary objectives

The secondary objectives and the corresponding end-points are:To determine the [^131^I]ICF01012 sensitivity and specificity in a patient-based analysis and in a lesion-based analysis.[^131^I]ICF01012 sensitivity and specificity in patient-based analysis and in lesion-based analysis will be quantified by comparison of visualized or non-visualized lesions with [^131^I]ICF01012 imaging compared to metastatic lesions objectified by standard imagery (TEP-TDM or TDM) and or clinical evaluation.To evaluate the tolerance of [^131^I]ICF01012. [^131^I]ICF01012 tolerance (acute and delayed toxicities) will be evaluated with the Common Terminology Criteria for Adverse Events (CTCAE, version 4.03) with a special consideration for skin-related, ocular and neurological toxicities. Tolerance assessments include: Clinical examination with vitals (heart rate, blood pressure, temperature, respiratory rate), weight, height, OMS performance status; Cardiac evaluation (myocardial perfusion scintigraphy with measure of left ventricular ejection fraction (LVEF), Electrocardiogram (ECG); Specialised consultation with dermatologist, neurologist and ophthalmologist (with of a dilated fundus examination); Blood test including Fool blood count, prothrombine time, factor V, sodium, potassium, chloride, calcium, phosphore, bicarbonate, serum total protein, serum albumin, fasting blood glucose level, Thyroid-stimulating hormone (TSH), free thyoroxine (fT4), free triiodothyronine (fT3), creatinine, urea, bilirubin, Alkaline phosphatase (ALP), Gamma-glutamyltransferase (GGT), Aspartate amino transferase (AST or SGOT), Alanine amino transferase (ALT or SGPT), Troponin Lactate dehydrogenase (LDH); 24-h urine collection tests: glucose, urea, creatinine, albumin, sodium, potassium, magnesium, calcium, protein electrophoresis. Reporting of serious adverse events and suspected unexpected serious adverse reaction will be carried out according to the local regulations.To evaluate the pharmacokinetics of [^131^I]ICF01012 including the study of biodistribution and excretion.Variations of [^131^I]ICF01012 radioactivity concentration (AUC, Tmax and Cmax) will be measured on whole blood plasma during 8 days after diagnostic dose. Plasmatic free fraction of [^131^I]ICF01012 will be quantified by radioactive counting for each patient.24-h urinary excretion will be measured by counting.The biodistribution will be assessed with planar scintigraphy by measuring the percentage of [^131^I]ICF01012 injected dose absorbed by target and non-target organs for both diagnostic and therapeutic doses.To assess the therapeutic response of [^131^I]ICF01012. Therapeutic response (objective response rate, rate of clinical benefit, progression-free survival) will be assessed by TDM according to RECIST 1.1 criteria and by [^18^F] FDG TEP/TDM according to PERCIST criteria.To evaluate the correlation between therapeutic response, injected dose and tumoral uptake.To evaluate the personalized dosimetry applied to [^131^I]ICF01012, and its interindividual variability, Absorbed dose for each organ will be assessed by MIRD formalism.To compare the therapeutic recommended dose with the dose calculated with personalized dosimetry;To compare biodistribution of diagnostic dose and therapeutic dose.

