**Methods:**

The MELRIV-1 trial is an open-label, multicentric, dose-escalation phase I trial. The study is divided in 2 steps, a selection part with an IV injection of low activity of [^131^I]ICF01012 (185 MBq at D0) to select patients who might benefit from [^131^I]ICF01012 TRT in therapeutic part, i.e. patient presenting at least one tumour lesion with [^131^I]ICF01012 uptake and an acceptable personalized dosimetry to critical organs (liver, kidney, lung and retina). According to dose escalation scheme driven by a Continual Reassessment Method (CRM) design, a single therapeutic injection of 800 MBq/m^2^, or 1600 MBq/m^2^, or 2700 MBq/m^2^ or 4000 MBq/m^2^ of [^131^I]ICF01012 will be administered at D11 (± 4 days). The primary endpoint is the recommended therapeutic dose of [^131^I]ICF01012, with DLT defined as any grade 3-4 NCI-CT toxicity during the 6 weeks following therapeutic dose. Safety, pharmacokinetic, biodistribution (using planar whole body and SPECT-CT acquisitions), sensitivity / specificity of [^131^I]ICF01012, and therapeutic efficacy will be assessed as secondary objectives. Patients who received therapeutic injection will be followed until 3 months after TRT. Since 6 to 18 patients are needed for the therapeutic part, up to 36 patients will be enrolled in the selection part.

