## Methods/design

### Study design

This is an open-label, multicentric, “first-in-human”, dose-escalation phase I trial of a radiopharmaceutical.

The study based on a theranostic approach is divided in 2 steps:Firstly, a “selection part”, to determine if the patient is eligible for therapy, i.e., if the radiopharmaceutical is up-taken by metastases. During this phase, a single IV injection of low activity of [^131^I]ICF01012, called “diagnostic dose” will be injected to the patient. Pre-treatment dosimetry allows to measure for each patient the absorbed dose by organs and tissues. Patients will be eligible for the second step, the “therapeutic part” if they present at least one tumor lesion with [^131^I]ICF01012 uptake and if mean absorbed dose (AD) to liver < 26 Gy, kidney AD < 16.2 Gy, lung AD < 15 Gy et retina AD < 40 Gy.Secondly, a “therapeutic part” consisting of a single IV injection of [^131^I]ICF01012 at a therapeutic activity. The dose escalation will be driven by a Continual Reassessment Method (CRM) [27] with 4 [^131^I]ICF01012 activity levels: 800, 1600, 2700, or 4000 MBq/m^2^.

The duration of intervention for each patient will be 7 days (diagnostic phase only) or 3 weeks (diagnostic phase + therapeutic phase). Follow-up will last 4 weeks (diagnostic phase only) or 10 weeks (diagnostic phase + therapeutic phase).

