Hematology and coagulation	✓			✓	✓				✓	✓	✓	✓	✓	✓		✓
Blood chemistry	✓			✓	✓		✓		✓	✓	✓	✓	✓	✓		✓
Thyroid function	✓					✓							✓	✓		✓
Urinalysis	✓					✓	✓		✓	✓	✓	✓	✓	✓		✓
Pharmacokinetic sample		✓Before, 5, 10, 15, 30 min, 1 h, 3 h after														
[131I]ICF01012		✓ 185 MBq				✓ TI^a^										

^a^a single therapeutic injection (TI) of 800 MBq/m^2^, or 1600 MBq/m^2^, or 2700 MBq/m^2^ or 4000 MBq/m^2^ of [131I]ICF01012

Before any study-related assessment starts, written informed consent will be obtained for each patient. A screening/baseline visit will include imaging for disease evaluation and a dosimetric whole-body CT-scan within 30 days before administration of the diagnostic dose (D0). Within 15 days before administration of the diagnostic dose, the patients will have a clinical evaluation with vital signs, cardiac evaluation, specialized consultation with a dermatologist, a neurologist and an ophthalmologist, blood and urine test and a pregnancy test (for women of childbearing age).

Patients are registered before the diagnostic dose (D0).

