##### Follow-up

Non-eligible patients for therapeutic part will be followed during 3 weeks: 2 follow-up visits are scheduled 14 days and 35 days after diagnostic dose injection for safety evaluation (clinical examination, vital measurement, blood and urinary analyses, specialized consultations (ophthalmologist, neurologist and dermatologist)).

For patient receiving the therapeutic dose, five follow-up visits are scheduled 14, 28, 42, 63 and 85 days after therapeutic dose injection. Each visit will include: clinical examination, vital measurement, blood and urinary analyses. Specialized consultations (ophthalmologist, neurologist and dermatologist) will occur 14 days after therapeutic dose and for dermatologist consultations 42 and 85 after therapeutic dose. Dosimetric acquisitions will be done on 14 and 63 after therapeutic dose (see below). Post-therapeutic cardiac evaluation (myocardial perfusion scintigraphy) and disease staging (cranial and thoraco-abdominopelvic CT scan and [^18^F] FDG PET-CT) will be done 85 days after therapeutic dose.

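### One post-treatment tumour assessment, at the last visit, supports a progression-free proportion at day 85 but not a reliable progression-free survival time

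*Protocol article*

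**What the plan says.** Under *Secondary objectives*, the protocol article makes PFS one of three measures of therapeutic response and fixes the instruments: "Therapeutic response (objective response rate, rate of clinical benefit, progression-free survival) will be assessed by TDM according to RECIST 1.1 criteria" (TDM is CT), and FDG PET-CT by PERCIST.

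The *Follow-up* section says of patients who receive the therapeutic dose that "five follow-up visits are scheduled 14, 28, 42, 63 and 85 days after therapeutic dose injection". The content common to these visits is not tumour imaging: "Each visit will include: clinical examination, vital measurement, blood and urinary analyses". Staging with the two named instruments appears once: "disease staging (cranial and thoraco-abdominopelvic CT scan and [^18^F] FDG PET-CT) will be done 85 days after therapeutic dose".

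Table 2 agrees. Its disease evaluation row is ticked only at screening and at D96 ± 4. The pre-treatment assessment is described as follows: "A screening/baseline visit will include imaging for disease evaluation and a dosimetric whole-body CT-scan within 30 days before administration of the diagnostic dose (D0".

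The abstract gives the end of observation: "Patients who received therapeutic injection will be followed until 3 months after TRT". No later imaging or survival follow-up is described.

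**The concern.** A PFS time needs progression to be looked for repeatedly, so that its date is known to within a short interval. Here the named criteria are applied once after treatment, on the day observation ends. A patient whose disease progressed on imaging at week 3 and one whose disease progressed at week 11 would both be recorded as progressing at about day 85. Patients still progression-free at that scan contribute nothing later.

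A PFS time summarised from such data would largely reflect the scan date, and it would err in the favourable direction. The article also plans to relate therapeutic response to injected dose and tumour uptake. PFS times mostly tied at one date would add little to that analysis beyond a yes/no status.

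**Working it through.** **1. The schedule.** In Table 2 the therapeutic injection is at D11 and the post-treatment evaluation at D96. 96 − 11 = 85 days, which reproduces the figure in *Follow-up*. Day 85 is the last of the five visits.

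**2. Other scans.** The acquisitions at days 14 and 63 are called dosimetric in *Follow-up*, and *Therapeutic part* describes them as planar scintigraphy and SPECT of the radioligand. They are not the CT or FDG PET-CT on which the endpoint is defined. The previous response scan is the baseline one, up to 30 days before D0, so nominally up to 30 + 11 = 41 days before the injection.

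**3. Size of the distortion.** The article states no PFS median or rate, so the true median m is an assumption and is varied. PFS is taken as exponential from the injection, with λ = ln 2 / m.

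- Proportion progression-free at day 85: S = 0.5^(85/m).
- True restricted mean to day 85: (1 − S)/λ.
- With every progression dated at the scan, the restricted mean is 85.0 days whatever m is. The median is 85 days if S is below 0.5 and is otherwise not reached.
- With 20% of events dated exactly, the restricted mean is 85·S + (1 − S)(0.2·t + 0.8·85). Here t is the mean event time among those progressing before day 85.

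For m = 60: S = 0.375, t = 35.7 and the true restricted mean is 54.1. The 20% variant gives 31.9 + 0.625 × 75.1 = 78.8.

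| Assumed true median (days) | S at day 85 | Median, all dated at scan | Excess | True restricted mean | Restricted mean, 20% dated exactly | Mean dating delay, all at scan |
|---|---|---|---|---|---|---|
| 42 | 0.246 | 85 | 85/42 = 2.02, 102% | 45.7 | 77.1 | 52.1 |
| 60 | 0.375 | 85 | 85/60 = 1.42, 42% | 54.1 | 78.8 | 49.3 |
| 75 | 0.456 | 85 | 85/75 = 1.13, 13% | 58.9 | 79.8 | 48.0 |
| 90 | 0.520 | not reached | – | 62.4 | 80.5 | 47.1 |
| 120 | 0.612 | not reached | – | 67.2 | 81.4 | 46.0 |

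**4. At the planned maximum size.** The check used 18 treated patients, a ±4-day scan window, 20,000 simulated trials and the ninth ordered time as the median.

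| Assumed true median (days) | Typical median, exact dating | Typical median, scan dating | Not reached |
|---|---|---|---|
| 42 | 38.6 | 86 | 1% |
| 60 | 55.5 | 87 | 9% |
| 75 | 69.7 | 88 | 27% |
| 90 | 83.6 | 89 | 47% |
| 120 | not reached | not reached | 77% |

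Dating 20% of events exactly changes the scan-dated medians by at most one day (85, 87, 88 and 89 in the first four rows).

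**5. How much earlier dating would be needed.** The estimated median stays at the scan date while fewer than half of the patients have an event dated before it. In expectation, the share of events dated early must reach 0.5/(1 − S) to move it: 0.5/0.754 = 66% for m = 42, 0.5/0.625 = 80% for m = 60, and 0.5/0.544 = 92% for m = 75.

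**6. What is not distorted.** S at day 85 depends only on whether progression has occurred by then, not on its date. The one scan estimates it directly.

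**The case against.** The best defence is that the article commits to no analysis of PFS time. It mentions neither Kaplan-Meier nor a median, calls the analysis mainly descriptive, and names PFS in a bracket beside two rates. That wording is compatible with a progression-free rate at the final evaluation, and the definition may sit in the full protocol or the SAP. This stands in part: a reader might infer that a median PFS is planned, and the document does not say so. But no definition elsewhere can supply scans that are not scheduled, and the schedule is given in both text and table. The label as written promises more than the schedule can deliver.

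Second, a reader might infer that PFS data would be nothing but one step at day 85. The documents do not support that. Patients are seen on days 14, 42 and 63, and day 28 is also a scheduled visit. Dermatology consultations fall on days 14 and 42, so deaths and clinically evident progression can be dated earlier. Step 5 shows that most events would have to be dated this way before the median moved.

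Third, no single percentage can be called the bias, because the true median is unknown. Nor is the estimate always 85 days or not reached. With 6 treated patients and 62.5% progressing, fewer than three progress in 0.003 + 0.028 + 0.116, about 15%, of trials, so the median is then not reached even though the true median is 60 days. Conversely, at a true median of 120 days a value is still produced in 23% of trials of 18.

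Finally, the statement that "Follow-up will last 4 weeks (diagnostic phase only) or 10 weeks (diagnostic phase + therapeutic phase" might suggest that follow-up stops before the day-85 scan. Counted from the first follow-up visit in Table 2 it does not: D96 − D25 = 71 days, about 10 weeks.

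**Conclusion.** The point holds in a limited form. With one RECIST/PERCIST assessment after treatment, at the last visit, the schedule yields progression-free status at about day 85. It does not yield a reliable PFS time or median, and any such time would be biased upward. The direction follows from the schedule alone. The size rests on an assumed exponential PFS with all progression dated at the scan: 13% to 102% too long for true medians of 75 down to 42 days, and usually no median at all when the true median is well above 85 days. The claim that PFS cannot be estimated in any sense goes too far, since the day-85 proportion is estimable and undistorted by the dating.

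Severity is minor. PFS is one of several secondary measures in a descriptive phase I trial of 6 to 18 treated patients. The recommended dose rests on dose-limiting toxicity within 6 weeks of the therapeutic injection and is not affected.

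**What to change.** In *Secondary objectives*, replace progression-free survival by the proportion of treated patients alive and progression-free at day 85 after the therapeutic injection, with an exact binomial interval. Count death or documented clinical progression before day 85 as failure. Report no median PFS.

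This changes wording only: no scan, visit or patient is added. The cost is the loss of the PFS time label.

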
### Patients

#### Inclusion criteria

Patient with metastatic melanoma failure to recommended treatments by French Health AuthorityInitial histological diagnosis of cutaneous melanoma pigmented or unknown status or choroidal melanomaPresence of at least one measurable lesion and / or evaluable in 18FDG-PET as PERCIST criteriaPresence of at least one measurable lesion and / or evaluable as CT RECIST 1.1 criteriaWHO performance index ≤2Age > 18 yearsLife expectancy > 3 months

#### Exclusion criteria

Symptomatic brain metastasesPatient with a VI skin phototypePrevious treatment with chemotherapy, radiotherapy, immunotherapy and targeted therapy in the previous 4 weeks, the first injection of [^131^I]ICF01012Pregnant woman, nursing or woman of childbearing age refusing to follow effective contraception during treatment and 12 months after the administration of therapeutic doseMan refusing to follow effective contraception during treatment and 12 months after the administration of therapeutic doseOther evolutionary known cancer in the past 5 yearsEarlier irradiation of more than 25% of the bone marrowSuspicion of invasion of more than 25% of the bone marrow on imaging 18F-FDG PET-CTExternal Radiotherapy on target organs or the maximum dose as recommended in forceUncontrolled diabetesKnown history of allergy to the excipients of the solution of [^131^I]ICF01012Any comorbidity or severe disease at the discretion of the investigator

### Intervention

#### Study drug

[^131^I]N-(2-diethylaminoethyl)-6-iodoquinoxaline-2-carboxamide ([^131^I]ICF01012) is a quinoxaline derivative radiolabeled with iodine-131. [^131^I]ICF01012 is synthesized by radio-iododestannylation in presence of hydrogen peroxide as oxidative agent. Production takes place in the radiopharmacy unit of the Jean Perrin Center. For radiation protection, the synthesis is carried out entirely on an AIO® synthesizer (TRASIS).

The experimental drug is an injectable solution of [^131^I]ICF01012 (mixture of 0.9% NaCl saline solution and ethanol / water). The maximum injectable volume is 10 mL. The radiochemical purity of radiolabeled [^131^I]ICF01012 is required to be over 95% before injection.

#### Study drug and premedication administration

##### Selection part

The diagnostic dose of [^131^I]ICF01012 labeled with an activity of 185 MBq will be administered by slow intravenous injection in a approximatively 10 min at D0 in the presence of a nuclear medicine physician.

Patients will receive per os premedication of potassium iodide 130 mg of 48 h before [^131^I]ICF01012 injection, and of loratadine 10 mg and potassium iodide 130 mg, 24 h before [^131^I]ICF01012 injection. The day of the injection, oral potassium iodide 130 mg will be taken approximatively 4 h before injection and IV premedication (dexchlorpheniramine 5 mg and hydrocortisone hémisuccinate 500 mg) 5 minutes before injection. Thyroid blockade will be pursued for a period of 8 days (D1-D8) (potassium iodide 130 mg daily).

##### Therapeutic part

According to the dose escalation scheme, a single therapeutic injection of 800 MBq/m^2^, or 1600 MBq/m^2^, or 2700 MBq/m^2^ or 4000 MBq/m^2^ of [^131^I]ICF01012 will be administered at D11 (± 4 days) under the same conditions as those for diagnostic injection (slow IV injection in approximatively 10 min).

Before therapeutic injection of [^131^I]ICF01012, patients will receive identical premedication as for the diagnostic injection: potassium iodide 130 mg at 48 h before infusion, loratadine 10 mg and potassium iodide 130 mg 24 h before injection. The day of the injection, oral potassium iodide 130 mg will be taken approximatively 4 h before injection and IV premedication (dexchlorpheniramine 5 mg and hydrocortisone hémisuccinate 500 mg) 5 minutes before injection. Thyroid blockade will be pursued for a period of 60 days (D12-D71) (potassium iodide 130 mg daily).

#### Study procedures and participant timeline

The overview of study assessments and procedures is detailed in Table 1 for patients who participate only to the selection part, and in Table 2 for patients who participate to the selection part and the treatment part.

**Table 1 Tab1:** Assessment schedule for patients who received diagnostic injection and were not eligible to therapeutic part

TIMEPOINT	Screenig / baseline	Selection part			Follow-up period		
Week		W0			W1	W2	W3
Day	−30 to −1	D0	D1	D4	D7	D14 ± 4	D35 ± 4
Informed consent	✓						
Medical history and demographic	✓						
Prior / concomitant medication	✓	Collecting during all the study					
Adverse event evaluation	✓	Collecting during all the study					
Physical exam	✓	✓	✓	✓	✓	✓	✓
Vital signs	✓	✓before, 5 min, 30 min, 1 h, 3 h after	✓	✓	✓	✓	✓
Performance status OMS	✓	✓			✓	✓	✓
ECG	✓						✓
LVEF	✓						
Dermatologist consultation	✓					✓	
Ophthalmologist consultation	✓					✓	
Neurologist consultation	✓					✓	
Imaging acquisition for dosimetry		✓30 min, 1 h, 3 h after	✓	✓	✓		
Disease evaluation	✓						
Pregnancy test	✓						
Hematology and coagulation	✓			✓	✓	✓	✓
Blood chemistry	✓			✓	✓	✓	✓
Thyroid function	✓						✓
Urinalysis	✓					✓	✓
Pharmacokinetic sample		✓Before, 5, 10, 15, 30 min, 1 h, 3 h after	✓	✓	✓		
[131I]ICF01012		✓ 185 MBq

**Table 2 Tab2:** Assessment schedule for patients who received diagnostic and therapeutic injection

TIMEPOINT	Screenig / baseline	Selection part				Therapeutic part						Follow-up period				
Week		W0				W1					W2	W3	W5	W7	W10	W13
Day	−30 to −1	D0	D1	D4	D7	D11 ± 4	D12 ± 4	D13 ± 4	D15 ± 4	D16 ± 4	D18 ± 4	D25 ± 4	D39 ± 4	D53 ± 4	D74 ± 4	D96 ± 4
Informed consent	✓															
Medical history and demographic	✓															
Prior / concomitant medication	✓	Collecting during all the study														
Adverse event evaluation	✓	Collecting during all the study														
Physical exam	✓	✓	✓	✓	✓	✓	✓	✓	✓	✓	✓	✓		✓	✓	✓
Vital signs	✓	✓ before, 5, 30 min, 1 h, 3 h after injection	✓	✓	✓	✓ before, 5, 30 min, 1 h, 3 h after injection	✓	✓	✓	✓	✓	✓		✓		✓
Performance status OMS	✓	✓			✓	✓	✓	✓	✓	✓	✓	✓		✓		✓
ECG	✓													✓		✓
LVEF	✓															✓
Dermatologist consultation	✓											✓		✓		✓
Ophthalmologist consultation	✓				OCT							✓OCT				✓
Neurologist consultation	✓											✓				
Imaging acquisition for dosimetry		✓30 min, 1 h, 3 h after	✓	✓	✓				✓		✓	✓			✓	
Disease evaluation	✓															✓
Pregnancy test	✓															
Hematology and coagulation	✓			✓	✓				✓	✓	✓	✓	✓	✓		✓
Blood chemistry	✓			✓	✓		✓		✓	✓	✓	✓	✓	✓		✓
Thyroid function	✓					✓							✓	✓		✓
Urinalysis	✓					✓	✓		✓	✓	✓	✓	✓	✓		✓
Pharmacokinetic sample		✓Before, 5, 10, 15, 30 min, 1 h, 3 h after														
[131I]ICF01012		✓ 185 MBq				✓ TI^a^										

^a^a single therapeutic injection (TI) of 800 MBq/m^2^, or 1600 MBq/m^2^, or 2700 MBq/m^2^ or 4000 MBq/m^2^ of [131I]ICF01012

Before any study-related assessment starts, written informed consent will be obtained for each patient. A screening/baseline visit will include imaging for disease evaluation and a dosimetric whole-body CT-scan within 30 days before administration of the diagnostic dose (D0). Within 15 days before administration of the diagnostic dose, the patients will have a clinical evaluation with vital signs, cardiac evaluation, specialized consultation with a dermatologist, a neurologist and an ophthalmologist, blood and urine test and a pregnancy test (for women of childbearing age).

Patients are registered before the diagnostic dose (D0).

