#### Data analysis

Due to the nature and the design of the study, statistical analysis will be mainly descriptive. Two populations will be analyzed: the diagnostic population (all participants who receive the diagnostic dose) and the therapeutic population (all participants who receive the therapeutic dose). The recommended therapeutic dose will be defined as the highest tested dose for which the percentage of DLT in the diagnostic population is lower than 33%. DLT percentage will be calculated for each tested dose. Only therapeutic population will be included in the analysis of DLT and the efficacy analysis. The statistical significance threshold is set at 5%. Statistical analyses will be performed using R software.

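### Baseline tumour imaging is timed from the diagnostic dose, so it can be 8 to 45 days old at the therapeutic injection whose effect it is meant to measure

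*Protocol article*

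**What the plan says.** Under Study procedures and participant timeline, the article states: "A screening/baseline visit will include imaging for disease evaluation and a dosimetric whole-body CT-scan within 30 days before administration of the diagnostic dose (D0"; the screening column of Tables 1 and 2 gives the same range, day -30 to -1. The next sentence sets a shorter window for the clinical, cardiac, specialist and laboratory assessments, beginning "Within 15 days before administration of the diagnostic dose, the patients will have a clinical evaluation with vital signs". Tumour imaging is not in that list.

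The therapeutic injection "will be administered at D11 (± 4 days"), that is, on D7 to D15. Post-treatment staging by CT and FDG PET-CT "will be done 85 days after therapeutic dose". In Table 2 the disease-evaluation row is ticked only at screening and at D96 ± 4. The scans on D0 to D7 are on a separate row, for dosimetry.

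The Secondary objectives section states: "Therapeutic response (objective response rate, rate of clinical benefit, progression-free survival) will be assessed by TDM according to RECIST 1.1 criteria". PERCIST on FDG PET-CT is added, as is a correlation of response with injected dose and tumour uptake. The Exclusion criteria bar "treatment with chemotherapy, radiotherapy, immunotherapy and targeted therapy in the previous 4 weeks". I read the garbled end of that criterion as counting back from the first injection of the study product, which is the diagnostic dose at D0.

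**The concern.** A single-arm response assessment is a before/after comparison, and it is cleanest when the baseline scan lies close to the treatment being judged. Here the window is attached to the diagnostic dose, and the 7 to 15 days up to the therapeutic injection are added on top. With one baseline and one follow-up evaluation, whatever the tumour does between the scan and the injection is counted as part of the treatment's result.

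Patients enter after failing recommended treatments, so the likely change in the gap is growth. That makes response look poorer and progression more frequent than the therapeutic dose alone would justify. Scan age can also differ between patients by up to 37 days (45 - 8), which blurs the correlation of response with dose and uptake in only 6 to 18 treated patients. Separately, a 30-day imaging window combined with a 4-week washout does not guarantee that the baseline scan follows the end of prior therapy.

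**Working it through.** **Inputs.** Imaging window D-30 to D-1 (Study procedures; Table 2). Therapeutic injection D11 ± 4 (Therapeutic part). Follow-up imaging 85 days after the injection (Follow-up). Washout 4 weeks = 28 days before D0 (Exclusion criteria). Treated patients 6 to 18 (Sample size).

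**The plan's own calendar.** 11 + 14, 28, 42, 63 and 85 gives D25, D39, D53, D74 and D96, which are the follow-up days in Table 2. The calendar reproduces.

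**Scan age at the therapeutic injection.**
- Minimum: 1 + 7 = 8 days.
- Maximum: 30 + 15 = 45 days; at nominal D11, 30 + 11 = 41 days.
- If both windows were used uniformly (an assumption), the mean is 15.5 + 11 = 26.5 days.

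**Share of the comparison that precedes treatment.** With follow-up imaging exactly 85 days after injection, the interval runs from 8 + 85 = 93 to 45 + 85 = 130 days. The pre-treatment share at the maximum is 45/130 = 35%.

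**Overlap with prior therapy.** 30 - 28 = 2 days. A scan on D-30 or D-29 can precede a last prior treatment on D-28.

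**What the gap could mean for tumour size.** The documents give no growth rate, so volume doubling time (DT) is an assumption. Untreated growth in diameter over t days is 2^(t/(3 × DT)) - 1.

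| DT (days) | over 45 days | over 30 days |
|---|---|---|
| 60 | 18.9% | 12.2% |
| 90 | 12.2% | 8.0% |
| 120 | 9.1% | 5.9% |

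Over 45 days the figure is about 41% for a DT of 30 days and about 6% for a DT of 180 days.

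**Can scan age alone change a category?** Take a 20% increase in diameter as the progression cut-off, also an assumption because the article quotes none, and a tumour that the treatment does not affect. With a DT of 150 days (3 × 150 = 450):
- Growth in the 85 days after injection: 2^(85/450) - 1 = 14%.
- Measured from a scan 45 days old: 2^(130/450) - 1 = 22%.
- Measured from a scan 30 days old: 2^(115/450) - 1 = 19%.

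The same tumour is stable or progressive depending only on when it was scanned.

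**Effect of a limit at D-15.** The maximum age becomes 15 + 15 = 30 days and its share of the interval 30/(30 + 85) = 26%. The scan then falls at least 28 - 15 = 13 days after the end of prior therapy. Under uniform use the mean age falls from 26.5 to 8 + 11 = 19 days.

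**The case against.** The other side has several good points. The text and tables agree on the 30-day window, so this is a design choice and not a contradiction. D0 is the first administration of the product, which makes it a natural anchor. The 45 days is a worst case. Under uniform use, tightening to D-15 gains 7.5 days on average, about 2.9%, 1.9% or 1.5% of diameter for a DT of 60, 90 or 120 days. A fast tumour would progress whatever the window: with a DT of 60 days and no treatment effect, it grows 39% in the 85 days after injection. The endpoints concerned are secondary, and the article says that "statistical analysis will be mainly descriptive". A bias against the product is at least conservative. All of this stands and limits the weight of the point. What does not stand is that scan age can change no category; the 150-day example shows that it can for slower tumours.

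Three stronger readings are tempting, and the documents do not support them:
- *Baseline scans are taken on prior therapy and so confound response.* The overlap is at most 2 days and needs a scan on D-30 or D-29. Nothing links scan age to dose level or uptake, and there is no comparison group, so bias and noise are the right words. A late effect of prior therapy could work in the product's favour, but that depends mainly on the washout length.
- *The old scan is the sole reference for lesion sensitivity and specificity.* The Secondary objectives also allow clinical evaluation as reference, and physical examinations are scheduled at D0, D1, D4 and D7. A screening scan used as reference could be 30 to 37 days old, but no misclassification can be quantified.
- *One misclassified patient shifts the response rate by 5.6 points or more.* That is 1/18. It gives the weight of one patient and does not show that any patient is misclassified.

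**Conclusion.** The point holds as a moderate weakness in the secondary response endpoints. Three facts, all stated in the article, establish it: imaging is counted back from D0, the therapeutic injection comes 7 to 15 days later, and no disease evaluation lies in between. Scan age at injection can range from 8 to 45 days, and up to 35% of the baseline-to-follow-up interval can precede treatment. The expected direction is against the product, given a population that has failed prior treatment. The timing figures rest only on the stated windows, with follow-up taken at exactly 85 days; the growth figures rest on assumed doubling times and an assumed cut-off, and are illustrations. The primary endpoint, dose-limiting toxicity and the recommended dose, is not touched.

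**What to change.** In Study procedures and participant timeline, and in the screening column of Table 2:
- Anchor the disease-evaluation CT and FDG PET-CT to the therapeutic injection, with a maximum age of about 30 days. Because D15 is the latest injection day, this in practice means imaging within 15 days before D0, the window already used for the other baseline assessments.
- Require these scans to follow the last prior anticancer treatment. This closes the 2-day overlap; it does not remove late effects of that treatment.
- Report scan age at the therapeutic injection for each patient alongside response, including patients already enrolled, for whom the window can no longer be changed.

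The cost is protocol wording and some scheduling. Some scans must be booked later, and a few referral scans 16 to 30 days old at D0 may need repeating, with the burden of a second CT or PET-CT for those patients. No extra visits or patients are needed by design. Reporting scan age needs only the scan and injection dates and no new imaging, so it is worth doing even if the window is left as it is.
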